### Recruitment and randomisation of the participating sites

The local health authorities' Chief Executive Officers (CEOs) and GMF medical directors from all six territories of Abitibi-Témiscamingue agreed to participate in the study (response rate = 100%). Site randomisation will be done after the recruitment process of individual participants is completed, using a random allocation software [77]. Randomisation will be carried out by one of the researchers, with two independent observers present, and will be concealed to the professionals in charge of recruitment, the group facilitator, and participants until the end of the step 1 meeting (see Control section below).

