## Methodology

### Project overview and design

We will conduct a cluster randomised controlled trial that will assess the impact of public involvement on quality-indicator choice and intended use (Figure 1). A cluster design is warranted because of our interest in group decision making. In preparation for the trial, we have developed a 'menu' of validated quality indicators based on a systematic review of the literature and expert consultation. We also pilot tested our intervention and instruments. Participants (public representatives, clinicians, and managers) will be recruited from six participating sites, which will be randomised in intervention (quality-indicator prioritisation with public involvement) and control sites (without public involvement).

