### Study setting

Abitibi-Témiscamingue is one of the largest administrative regions of Québec, Canada, with a population of 145,886 people, including 6,500 people (4.5%) from First Nations communities. The economy of the region is centered around the mining and wood industry. Most of the population is francophone and 4% have English as their first language [46]. The Regional Health Authority of Abitibi-Témiscamingue (Agence de la santé et des services sociaux de l'Abitibi-Témiscaminge [ASSSAT]) is responsible for coordinating the services in the region. The region is divided into six local service networks, each one under the responsibility of a local health authority (Centre de santé et de services sociaux [CSSS]). The six local health authorities cover rural territories of a few thousand people with basic community care and medium-size towns of approximately 40,000 people with specialised hospital care. Local Health Authorities are responsible for ensuring access to health and social services for the population in its territory through direct service delivery and agreements with partner organisations in its local services network (medical clinics, community organisations, specialist services and hospitals, etc.) [47]. Most family physicians providing primary care services in the region are organised in family medicine groups (Groupes de Médecine Familiale [GMFs]), a group of family physicians working in close collaboration with nurses in an environment that fosters providing family medicine to registered individuals. Family physicians in the region cover many secondary care services (*e.g.*, emergency room, hospital care, obstetrical care, intensive care unit). Each local health authority is more than 100 km from another local health authority and serves a rather captive population that receives most of its care within its own community.

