### Step 2: group recommendations

In the step 2 meeting, public representatives, clinicians, and managers will deliberate together to agree on five local group recommendations. We will aim to recruit a total of 15 participants in each group (nine clinicians and managers and six public representatives). We will recruit public representatives from step 1 participants, based on their availability, interest, and natural attrition. If more people volunteer, the research team will select candidates based on our representation criteria to ensure a balanced representation of age, gender, employment, and health status (Table 2).

Group rating and deliberation on quality-indicator prioritisation will be done in four steps: (1) participants prioritise indicators individually at the beginning of the day; (2) feedback on individual responses is given to the whole group; (3) participants deliberate as a group on the indicators' pros and cons; (4) if consensus on group recommendations cannot be reached, the moderator asks participants to vote. At the end of the day, participants will be asked to agree on five indicators that they recommend using as targets for improvement in their territory (group recommendation). They will also be asked to record five indicators that they recommend individually. We will explain to the participants that it is not necessary for everybody to agree with the final group recommendations, as long as everyone can 'live with' the compromise or consensus reached by the group.

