### Sample size

Our sample size calculation is based on pragmatic considerations and takes into consideration the maximum number of available sites/clusters in the region (n = 6 sites) and the maximum number of recommended participants in small-group deliberation meetings (n = 15 participants per meeting). We aim to recruit a total of n = 90 public representatives, n = 72 clinicians and managers for the step 2 meeting, and n = 60 senior managers and professional council representatives for the step 3 meeting. We will allow for overlap between clinicians and managers participating in step 2 and step 3 meetings.

Abelson and colleagues note that small sample sizes are hard to overcome in studies of public participation in healthcare as 'deliberation decision-making dictates small groups' [13]. We expect that the power of our study will be further decreased by the cluster nature of the trial, although we are currently unable to estimate the magnitude of this effect due to the absence of prior trials of public involvement in quality-indicator prioritisation and unknown intra-cluster coefficients for our outcome of interest [93].

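### No restriction is described for allocating six very unlike sites, so all the hospital towns could fall in one arm (40% of 3:3 draws if there are two, 10% if there are three); a simple constrained draw would prevent this

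*Protocol article*

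**What the plan says.** The section on recruitment and randomisation of the participating sites gives the procedure in some detail. All six territories have agreed to take part. "Site randomisation will be done after the recruitment process of individual participants is completed, using a random allocation software". One researcher carries out the draw with two independent observers present, and the result is concealed from recruiters, facilitator and participants until the end of the step 1 meeting. No stratification, matching, constraint or allocation ratio is described there. The design overview says only that there are "six participating sites, which will be randomised in intervention (quality-indicator prioritisation with public involvement) and control sites (without public involvement".

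The Study setting section says of the sites that they "cover rural territories of a few thousand people with basic community care and medium-size towns of approximately 40,000 people with specialised hospital care", in a region "with a population of 145,886 people". It does not say how many sites are of each kind.

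The Sample size section fixes the number of clusters at "the maximum number of available sites/clusters in the region (n = 6 sites". The Statistical analysis section plans a descriptive comparison of the arms, calculates the agreement of professionals with the public at baseline and at the end of the trial, and allows for multilevel modelling if the data prove clustered.

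**The concern.** With six clusters, randomisation balances arms only on average over draws that will never be made; the single draw that is made can be badly lopsided. Here the most obvious site characteristic, size together with level of hospital care, is known for every site before the draw.

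It plausibly bears on the outcome. The indicator menu covers access to family physicians, coordination among organisations, and hospital and emergency visits for ambulatory-care-sensitive conditions. Professionals and public in a hospital town may agree on these to a different degree than those in a small rural territory, or may move by a different amount during deliberation. If all the towns are in one arm, such a difference is mixed with the effect of public involvement.

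Unlike the choice of a model, this cannot be left to an analysis plan, because the draw cannot be redone once the allocation is known.

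**Working it through.** **Inputs from the article.** Six sites (Sample size). Regional population 145,886 and towns of about 40,000 (Study setting). Step 2 groups of "a total of 15 participants in each group (nine clinicians and managers and six public representatives", against "the maximum number of recommended participants in small-group deliberation meetings (n = 15 participants per meeting". Step 2 target of 72 clinicians and managers (Table 2, Sample size).

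**Assumption 1: allocation ratio.** The article gives none. Nine clinicians and managers at every site would give 6 × 9 = 54, not 72. Nine at each of three intervention sites and a full group of 15 at each of three control sites gives 3 × 9 + 3 × 15 = 27 + 45 = 72. This suggests 3:3, but does not prove it, since 12 at every site also gives 6 × 12 = 72.

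**Assumption 2: number of hospital towns.** The text uses the plural, so at least two. Two towns leave 145,886 − 80,000 = 65,886 people for four sites; three leave 145,886 − 120,000 = 25,886 for three sites; four would need 160,000, more than the region holds. Two or three is therefore the working range. The averages left over, 65,886/4 = 16,472 or 25,886/3 = 8,629, are more than a few thousand, so some sites may lie between the two types.

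**Chance that all towns share an arm.** There are C(6,3) = 20 allocations at 3:3.

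- Two towns: both in a given arm leaves one further place for one of four sites, so 4 allocations per arm: 8/20 = 40%.
- Three towns: all in a given arm is 1 allocation per arm: 2/20 = 10%.

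If each site were instead allocated by an independent toss, the chances would be 2 × (1/2)² = 50% and 2 × (1/2)³ = 25%.

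**Cost of adjusting afterwards.** The arm is a site-level factor, so take a site-level linear model with six observations. Arm alone leaves 6 − 2 = 4 residual degrees of freedom (critical t 2.776). Adding one binary site-type covariate leaves 3 (critical t 3.182). The variance of the arm effect is multiplied by 1/(1 − r²), where r is the correlation between arm and site type:

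| Draw | r² | Variance multiplier |
|---|---|---|
| Two towns, split 1:1 | 0 | 1.0 |
| Two towns, same arm | 1/2 | 2.0 |
| Three towns, split 2:1 | 1/9 | 1.125 |
| Three towns, same arm | 1 | not estimable |

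For the same residual variance, the adjusted confidence interval with both of two towns in one arm is (3.182/2.776) × √2 = 1.62 times as wide as the unadjusted one. With the towns split it is 3.182/2.776 = 1.15 times as wide.

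**Effect of a constrained draw.** Keep only allocations in which the town counts differ by at most one between arms. The smallest two-sided permutation p is 2 divided by the number of allocations kept.

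| Towns | Allocations kept | Chance all in one arm | Smallest two-sided p |
|---|---|---|---|
| Unrestricted 3:3 | 20 | 40% (two), 10% (three) | 2/20 = 0.10 |
| Two, constrained | 2 × C(4,2) = 12 | 0 | 2/12 = 0.17 |
| Three, constrained | 20 − 2 = 18 | 0 | 2/18 = 0.11 |

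**The case against.** The strongest reply has four parts.

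- *The article is silent; it does not say the draw is unrestricted.* A condensed article may leave block or stratum settings to the full protocol, and the step 2 target points to a planned 3:3 split. This stands. A reader might infer that the sites will be allocated with no restriction at all, or without a fixed number per arm, but the text supports only that none is described.
- *Agreement is measured at baseline and against each site's own public.* This stands in part. A difference in level between town and rural sites can be offset by looking at change from baseline. A difference in how far the two kinds of site move is not.
- *Adjustment remains possible.* This also stands. A reader might infer that six sites leave no room to adjust, or that an imbalance could never be separated from the intervention effect. That is true only if all three of three towns share an arm. Otherwise one covariate can be fitted, at the price shown.
- *Nothing in the article shows that agreement differs by site type.* Correct. The link is an inference, and the article gives no figure for its size. It therefore cannot be said that an imbalance would be as large as the intervention effect.

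What remains is that a foreseeable imbalance can be ruled out at almost no cost before the draw and only at considerable cost after it.

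**Conclusion.** The point holds as a design improvement. No stated figure is wrong, and no passages contradict each other. The chance that all hospital towns fall in one arm is 40% with two towns and 10% with three, given a 3:3 split. Neither the number of towns nor the split is stated, so 40% should not be quoted alone. It is also an upper limit only under equal allocation. How much a lopsided draw would distort the result cannot be sized from the article, because it depends on an unknown difference between town and rural sites that remains after baseline is taken into account. The Sample size and Discussion sections acknowledge the small effective sample, but not chance imbalance between arms.

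**What to change.** In the section on recruitment and randomisation of the sites:

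1. State a 3:3 allocation.
2. Classify each site as hospital town or not, and record this before the draw, including how any intermediate site is classed.
3. List the 20 possible allocations and keep those in which the number of hospital-town sites differs by at most one between arms (equal if the number is even).
4. Draw one of these at random in front of the two observers already planned.
5. Record the retained set, so that any randomisation-based analysis uses it.

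Do not add a rule that picks the closest population totals unless it has a tolerance that keeps enough allocations. With unequal populations, such a rule could leave a single allocation and its mirror image.

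The cost is one paragraph and a short list made from known site data. Each site keeps a 50% chance of either arm, since every retained allocation has its mirror image in the set. The price is a coarser permutation test, with a smallest two-sided p of 0.17 (two towns) or 0.11 (three) in place of 0.10. The planned two-sided 0.05 level is out of reach for an exact permutation test of six sites either way, so no attainable exact significance is lost.

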### Individual participants' recruitment

Within each local health authority participating in the study, we created recruitment teams who are responsible for identifying public representatives, clinicians, and managers interested participating in the study. Each local recruitment team includes a member of the CSSS user committee, the manager in charge of the chronic disease program, and the medical director of the family medicine group. Local health authorities' CEOs will also be solicited to identify the managers and clinicians who will act as decision makers. Local recruitment teams will identify potential participants by purposive sampling and the snowballing technique, using our inclusion and representation criteria described in Table 2[78]. We seek to recruit clinicians and managers who are closer to healthcare delivery to participate in the step 2 meeting (group recommendations) and senior-level managers and professional council representatives for step 3 (decision makers' meeting), allowing for overlap between both meetings.

**Table 2 T2:** Inclusion and representation criteria

Category of participant	Inclusion/exclusion criteria	Representation criteria
**Public representatives** Steps 1, 2, 3 meetings (Target: 90 participants)	1) Adult with or without a chronic condition 2) Be competent to share opinions with others 3) Not be currently or previously working as a clinician or healthcare manager	Age, gender, employment, and health status (healthy adults without chronic disease, patients with uncomplicated chronic disease, patients with complex chronic conditions)

**Clinicians and managers** Step 2 meeting (Target: 72 participants)	1) Work as a clinician or manager in relation with the prevention or management of chronic diseases 2) Work within the catchment area of a participating health authority 3) Be competent to share opinions with others	Include a minimum of two primary care physicians, one manager familiar with the chronic disease program and existing information systems, and a balanced mix of clinicians and managers involved in chronic disease prevention and management

**Clinicians and managers** Step 3 decision makers' meeting (Target: 60 participants)	1) Be identified by the local health authority's CEO to advise him/her on the choice of quality indicator 2) Be a member of the board or professional council of the local health authority or family medicine group	Include the CEO or his/her representative, as well as one physician; the identification of other key decision makers is left to the CEO's discretion

CEO = chief executive officer.

For the purpose of our study, a public representative can include any adult targeted by the regional chronic disease prevention and management program who is not a healthcare professional or employee. This includes healthy adults, carers, and patients with chronic conditions. Interested individuals will be given a written description of the project and a 'job profile', explicitly stating that we are looking for people who represent a broad range of backgrounds and personal experiences and who are willing to work collaboratively with other public representatives, clinicians, and managers (Table 2). Identification of public representatives through local recruitment teams allows us to reach public members who have perceived legitimacy within their own community and who are interested in the issues discussed [79]. A research assistant will contact potential participants, confirm their eligibility criteria and interest/availability for participating in the study, and collect basic sociodemographic characteristics. The research team will select participants based on the representation criteria described in Table 2.

### Description of the intervention

The intervention is composed of three one-day meetings (step 1, step 2, and step 3) that aim at prioritizing local quality indicators. The Regional Health Authority expects that the selected indicators will be used to support continuous quality improvement of chronic disease prevention and management (rather than for external control or benchmarking), and each local health authority will be allowed to select its own indicators. The selected indicators will be integrated in the regional accountability contracts signed with each local health authority. Table 3 summarises the topics addressed in each intervention meeting, and their content is described in detail below.

**Table 3 T3:** Intervention meetings' content

Meetings	Participants	Content
**Step 1: Public representatives' training and recommendations**	Public representatives (Target: 15/site)	• Participants' discussion on positive and negative experience in relation to quality of care • Information on chronic disease and local prevention and management services • Explanation of the indicator menu and data collection on baseline public recommendations

**Step 2: Group recommendation**	Clinicians and managers (Target: 9/site) and public representatives (Target: 6/site)	• Individual baseline prioritisation • Deliberation on indicator choice ○ Block 1 (Structure: access and integration) ○ Block 2 (Process: technical quality and interpersonal care) ○ Block 3 (Outcome indicators) • Final group recommendation and individual recommendations

**Step 3: Decision makers' meeting**	Clinicians and managers (Target: 10/site) and public representatives (Target: 2/site)	• Expectations from the Regional Health Authority on quality-indicator choice and use • Presentation of recommendations issued in step 1 and step 2 meetings • Deliberation on indicator choice and implementation • CEOs summarise decisions and foresee actions for each local health authority

CEO = chief executive officer.

### Step 1: public representatives' training and recommendations

The step 1 meeting aims to train public representatives and to collect their individual recommendations for local quality improvement. Public representatives (target: 15 per site) will meet with the moderator for a one-day meeting. Participants will be asked in turn to reflect and share their experiences with and expectations toward quality of care, will receive background information on chronic disease and on existing prevention and management services in their community, and will receive explanations on the proposed quality indicators. At the end of the meeting, public representatives will individually prioritise the quality indicators and identify five indicators that they recommend as local targets for improvement (public baseline recommendations).

### Step 2: group recommendations

In the step 2 meeting, public representatives, clinicians, and managers will deliberate together to agree on five local group recommendations. We will aim to recruit a total of 15 participants in each group (nine clinicians and managers and six public representatives). We will recruit public representatives from step 1 participants, based on their availability, interest, and natural attrition. If more people volunteer, the research team will select candidates based on our representation criteria to ensure a balanced representation of age, gender, employment, and health status (Table 2).

Group rating and deliberation on quality-indicator prioritisation will be done in four steps: (1) participants prioritise indicators individually at the beginning of the day; (2) feedback on individual responses is given to the whole group; (3) participants deliberate as a group on the indicators' pros and cons; (4) if consensus on group recommendations cannot be reached, the moderator asks participants to vote. At the end of the day, participants will be asked to agree on five indicators that they recommend using as targets for improvement in their territory (group recommendation). They will also be asked to record five indicators that they recommend individually. We will explain to the participants that it is not necessary for everybody to agree with the final group recommendations, as long as everyone can 'live with' the compromise or consensus reached by the group.

### Step 3: decision makers' meeting

In the step 3 meeting, decision makers identified by the local health authority's CEO will choose which indicators to use as local targets for improvement and identify actions to implement these indicators in clinical practice and management. While step 1 and step 2 meetings will be held locally within each participating site, we will hold one semiregional step 3 meeting that will bring together decision makers from all intervention sites, and another semiregional meeting with all control sites. A semiregional format will allow us to involve senior directors from the Regional Health Authority and send consistent messages across all sites regarding the Regional Health Authority's expectations.

Local and regional recommendations developed in steps 1 and 2 meetings will be presented to decision makers. Individual recommendations will be communicated to decision makers by reporting the rank of each indicator, calculated from the proportion of participants who recommended each indicator. Group recommendations and individual recommendations will be color-coded to facilitate their identification by decision makers. Recommendations will be discussed in small-group deliberation sessions within each site. At the end of the meeting, each local health authority's CEO will summarise the decisions and actions proposed within his/her own territory. A Regional Health Authority representative (RL) will be present to explain the quality indicator expected use, describe the professional and technical resources that will be available to support quality-indicator implementation, and answer questions.

Public involvement in the step 3 meeting will combine consultation and deliberation methods. Decision makers will receive written feedback about individual recommendations made by public representatives in step 1 meetings (consultative component). Public representatives who participated in step 1 and step 2 meetings will also be invited to attend the meeting (target: two participants/site) to answer decision makers' questions and assist them in their choice (participation component).

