### Control

In control sites, quality-indicators prioritisation will be done by clinicians and managers only, following the format described for the above step 2 and step 3 meetings. Public representatives will not be involved in quality-indicator prioritisation.

For research purposes, we will also conduct step 1 meetings in all control sites to collect data on local public recommendations (see the Data Collection and Analysis sections below). The format and content of the step 1 meeting will be identical in control and intervention sites. The moderator and participants will be blinded to their allocation until the end of the meeting. We will present the results of this public consultation to control sites' decision makers at the very end of the step 3 meeting, after we collect all trial outcome data on quality-indicator choice and intended use.

The six participating sites are more than 100 km apart from one another, clinicians and managers have rare contact among themselves, and they serve rather captive populations who receive most of their care within their community, thus minimising the potential for contamination across intervention and control groups. We will ask all participants to respect the confidentiality of discussions and not to share any information in between meetings. We will assess for potential contamination among participants in all meetings.

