### Quality-indicator prioritisation

Our primary outcome is the comparison of indicator choice and agreement with public priorities between intervention and control groups. Data on quality-indicator prioritisation will be collected at baseline and at the end of each meeting (Figure 3). In order to collect public baseline priorities from all participating sites, we will hold step 1 meetings with public representatives from the six participating sites. Clinicians and managers' baseline priorities will be collected at the beginning of the step 2 meeting. Postdeliberation priorities will be collected at the end of the step 2 meeting. Decision makers' choice and final priorities will be collected at the end of the step 3 meeting. We will also collect postconsultation priorities from control site participants at the end of the step 3 meeting, after we collect data on decision makers' choice and intention to use and present results of public consultation. Postdeliberation and postconsultation priorities will be used for process evaluation purposes to assess the contribution of each component of the intervention.

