### Statistical analysis

Descriptive statistics will be used to summarise the characteristics of the study population and assess the comparability of intervention and control groups, as well as to summarise data on quality-indicator choice, intended use, and on the marginal costs of the intervention.

We will descriptively report which quality indicators are selected as targets for improvement within each site at the end of the trial and calculate the proportion that are in agreement with local public baseline priorities (ranks 1 to 5). Individual quality-indicator priorities will be analysed as a dichotomous measure by reporting the proportion of participants who selected each indicator as part of their five priorities and by calculating its rank (rank 1 = indicator selected by the greatest proportion of participants). Agreement with public priorities will be analysed by calculating the correlation between professionals (clinicians and managers) and public priorities at baseline and at the end of the trial (primary outcome). Cluster randomisation leads to a reduction of effective sample size and can give spurious statistical results if it is not accounted for properly [93,94]. We will check the data to assess the level of clusterisation within study sites and use appropriate cluster-level analysis (*e.g.*, multilevel modelling) if necessary. We will also compare decision makers' intention to use the selected indicators and participants' satisfaction between intervention and control sites. Statistical significance will be assumed at *p *< 0.05 (two-tailed test) for all tests.

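### End-of-trial outcomes are recorded in one shared step 3 meeting per arm, so meeting effects are confounded with arm and sites within an arm are partly dependent

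*Protocol article*

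**What the plan says.** All quotes are from the protocol article.

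- **Unit of randomisation.** Project overview and design describes "six participating sites, which will be randomised in intervention (quality-indicator prioritisation with public involvement) and control sites (without public involvement"). The allocation ratio is not stated.
- **Meeting format.** Step 3: decision makers' meeting keeps steps 1 and 2 local to each site and then plans the last step by arm: "we will hold one semiregional step 3 meeting that will bring together decision makers from all intervention sites, and another semiregional meeting", the latter for the control arm. The stated reason is to involve senior regional directors and give all sites the same message.
- **Shared content.** The same section says: "Local and regional recommendations developed in steps 1 and 2 meetings will be presented to decision makers". The Moderator section adds plenary sessions. Deliberation itself takes place in small groups by site.
- **Timing of the outcome.** Quality-indicator prioritisation: "Decision makers' choice and final priorities will be collected at the end of the step 3 meeting". Table 4 places this questionnaire (Q8), which also covers intention to use, at the end of step 3. The CEOs' summaries also come at the end of the meeting, and the order of the two is not given.
- **Primary outcome.** Statistical analysis: agreement is analysed by "calculating the correlation between professionals (clinicians and managers) and public priorities at baseline and at the end of the trial (primary outcome").
- **What is considered.** The Control section argues from distance between sites, "thus minimising the potential for contamination across intervention and control groups". Statistical analysis considers clustering within study sites, to be modelled if necessary. Post-deliberation priorities from step 2 (Q6 in Table 4) are assigned to process evaluation.

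**The concern.** Six sites are randomised and step 2 yields six separate group processes, but the final outcome comes from two gatherings. Sites in an arm hear the same presentations, sit in the same plenaries and see the same regional recommendations before the questionnaire is completed. A persuasive director, a lively or flat plenary, or an argument that travels between tables shifts all the sites of that arm. With one meeting per arm, such a shift looks exactly like an effect of public involvement.

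The safeguards in the protocol do not reach this. The distance argument concerns contact between arms, and step 3 removes that distance within an arm. The clustering provision concerns sites, not meetings. The limitation in the Discussion (small effective sample size) does not mention the shared meeting. At stake is the validity of the error rate and the interpretation of the primary comparison. It can be changed only before the step 3 meetings take place.

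**Working it through.** **1. Sites per arm (inferred).** Table 3 targets nine clinicians and managers and six public representatives per step 2 group, and the text aims for 15 participants per group. Suppose intervention groups have 9 professionals and control groups 15. With k intervention sites the total is 9k + 15(6 − k). The stated target of 72 gives 90 − 6k = 72, so k = 3. The other targets also reproduce: 15 × 6 = 90 public representatives and 10 × 6 = 60 step 3 decision makers. A 3 v 3 split is used below.

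**2. Is a meeting effect estimable?** Two meetings less two arm means leaves 0 degrees of freedom for meeting-to-meeting variance. No model can separate meeting from arm. This step needs no assumption beyond the stated format.

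**3. What a site-level test would miss.** Let s² be the variance between sites within a meeting and m² the variance of the meeting effect. For a difference between two arm means of three sites each:

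- true variance = 2s²/3 + 2m²
- variance the t-test estimates (4 df) = 2s²/3
- ratio = 1 + 3m²/s²

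The true type I error at nominal 5% two-sided is P(|t₄| > 2.776/√(1 + 3m²/s²)). With f = m²/(m² + s²), the effective number of independent sites per arm is 3/(1 + 2f).

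| m²/s² (assumed) | f | Effective critical value | Type I error | Effective sites per arm |
|---|---|---|---|---|
| 0 | 0 | 2.776 | 0.050 | 3.0 |
| 0.10 | 0.09 | 2.435 | 0.072 | 2.5 |
| 0.25 | 0.20 | 2.099 | 0.104 | 2.1 |
| 0.50 | 0.33 | 1.756 | 0.154 | 1.8 |
| 1.00 | 0.50 | 1.388 | 0.237 | 1.5 |

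A simulation with 200,000 runs gave 0.104 at f = 0.20 and 0.237 at f = 0.50, in agreement with the formula.

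**4. Individual-level illustration.** With 10 decision makers per site and an assumed site ICC of 0.05, meeting ICCs of 0.02, 0.05 and 0.10 give type I errors of 0.08, 0.12 and 0.20 for a site-level test, and 0.17, 0.26 and 0.38 if clustering is ignored (20,000 runs each).

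The protocol gives no variance components; Sample size calls the intra-cluster coefficients unknown. The variance ratios are therefore assumptions. The 4-df t-test is a reference analysis, because the article names multilevel modelling only as an example.

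**The case against.** **The sites remain largely separate.** Recommendations are discussed in small groups by site, each authority selects its own indicators, each CEO speaks for one territory, and site choices are compared with local public priorities. This stands. A reader might infer that there is effectively one cluster per arm. As a statement of sample size the protocol does not support that: even at the top of the assumed range, 1.5 effective sites per arm remain. The dependence is partial.

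**Much of the day is standardised.** The same professional moderator runs the plenaries with a prepared grid, the same research team member presents, and control follows the same format. This reduces m² but does not make it zero, since group dynamics and exchange between sites are not scripted.

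**Public presence at step 3 is the intervention.** Agreed. The concern is with everything else particular to that meeting.

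**Control sites might be shown intervention-site results.** A reader might infer this from the undefined word *regional*. The protocol does not say so. It excludes the public from control prioritisation, withholds even the control sites' own public results until outcomes are collected, asks participants for confidentiality and plans to assess contamination. The wording needs clarifying; it is not evidence of a leak.

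**Strong inference was never available.** Sample size calls the numbers pragmatic, and with 3 v 3 sites the smallest two-sided permutation p-value is 2/20 = 0.10. This tempers what the trial could claim, but the article still sets p < 0.05 for all tests and does not name this source of error.

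**Conclusion.** The point holds in a limited form. Confounding of meeting with arm follows directly from the stated format, and neither the contamination argument, the clustering provision nor the limitations address it. Sites within an arm are partly dependent to an unknown degree. The 7% to 24% range is correct arithmetic on assumed variance ratios and an inferred 3 v 3 split; it illustrates sensitivity and does not estimate the actual error. The joint format has a stated and reasonable purpose, so the remedy should preserve that purpose and limit the inferential cost.

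**What to change.** 1. **Step 3 agenda.** Keep the Regional Health Authority's opening messages, identical in both arms. Collect each site's decision and Q8 directly after its within-site session, before any cross-site discussion and before the CEOs' summaries.
2. **Supporting analysis.** Prespecify the six-site comparison of professionals' end-of-step-2 priorities (Q6), which come from six separate meetings, as a key supporting analysis rather than process evaluation only. State that it reflects the participation component alone and partly different professionals. Agreement in direction alone is weak support: with no true effect, an independent comparison would agree half the time.
3. **Wording.** State that regional recommendations shown in control sites come only from control-site clinicians and managers.
4. **Limitation.** Step 1 above reduces the dependence but does not remove it, because sites still share a meeting. State the remaining meeting-arm confounding, and do not present the step 3 p-value alone as confirmatory.

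The cost is a small agenda change and one extra analysis of data already collected.
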